## Abstract

International research on nursing skill mix has focused primarily on medical and surgical patient populations. The association between nursing skill mix and clinical outcomes for psychiatric inpatients has not been explored. The aim of this study is to establish the feasibility of extracting and linking nurse and inpatient data from hospital administrative data sources. This is an observational study. Data will be extracted from hospital administrative sources and linked together. Patient information will include duration and number of psychiatric hospital admissions. We will extract information on the educational preparation of nurses working in the participating hospitals to enable us to calculate estimates of the nursing skill mix. The study will be conducted in two psychiatric inpatient services in Australia. Our study will test the feasibility of extracting and linking nursing skill mix and patient data in a mental health setting and will inform the methodological development of an appropriately powered observational study. **Australian and New Zealand clinical trial registry:** ACTRN12619001337167p.

## 1. Introduction

### 1.1. Mental Health Nursing Workforce

There is considerable variation in the skill mix of nurses working in mental health settings. Some countries have a blend of registered nurses and those with specific mental health nurse education, this is the model in Australia [1]. In other countries, such as the United Kingdom, wards are staffed entirely by mental health nurses [2].

The World Health Organisation (WHO) estimates that in 2020 there were 3.8 nurses per 100,000 people working in mental health settings globally [3]. The WHO regions and income groups differed widely. For example, the Western Pacific Region had 5.3 nurses per 100,000 people, while the European Region had 25.2 nurses per 100,000 persons. Similarly, low-income nations had 0.4 nurses per 100,000 people, whereas high-income countries had 29 nurses per 100,000 [3]. It’s worth noting that the WHO makes no mention of the number of nurses who are specifically trained in mental health nursing. In 2019, Australia had 90.2 full-time equivalents (FTEs) mental health nurses per 100,000 population [4].

### 1.2. Nursing Education and Patient Outcomes

The association between nursing education and patient outcomes (mortality, medication errors) in medical and surgical settings has been extensively studied [5,6,7,8]. Most authors report that a more highly qualified nursing workforce is associated with lower odds of mortality. For example, Lasater et al. [8] conducted an observational study using data from two cross-sections in time (2006, 2016) to examine if changes in hospital employment of nurses with bachelor’s degrees over time were associated with differences in patient outcomes in surgical wards of 519 hospitals. The authors used a nurse survey, American Hospital Association Annual Survey, and patient administrative claims to collect data. Patients in hospitals with a higher proportion of nurses with bachelor’s degrees had lower risk-adjusted mortality, 7-day and 30-day readmission rates, and shorter hospital stays [8].

### 1.3. Mental Health Nursing Education

The definition of a mental health nurse differs from country to country. For example, in the United States of America and Australia, nurses complete a “comprehensive” qualification that would enable them to work in any clinical setting, including mental health [9,10,11]. Nurses may then go on to complete specialist mental health nurse education [10,11].

In the United Kingdom, there is a direct pathway into mental health nursing. Registrants in this field of practice are only licenced to work clinically in mental health settings [12]. Because of the nursing skill mix–comprehensive nurses and nurses with postgraduate education-in the Australian mental health system, there is the potential to calculate a comprehensive to mental health nurse ratio.

### 1.4. Mental Health Nurse Education and Patient Outcomes

We have previously reported a systematic review of observational and experimental studies that tested the association between mental health nurse skill mix and patient outcomes (relapse of illness) in a psychiatric inpatient setting [13]. We found no studies that tested this association, suggesting a gap in knowledge. Prior to undertaking a full-scale appropriately powered observational study, there is a need to establish the feasibility of undertaking such research.

### 1.5. Outcomes in Mental Health Skill Mix Research

Mortality is typically used as an outcome in skill mix research in medical and surgical settings. The use of mortality as an outcome in mental health is problematic. Death in inpatient settings is a rare event [14]. Consequently, it should not be considered a meaningful or practical outcome for use in mental health skill mix research.

The need for further inpatient admissions is common for people experiencing mental-ill health. For example, in one multi country study, more than 15% of people with schizophrenia required readmission to psychiatric inpatient units within 30 days of discharge [15]. Relapse of mental-ill health is the most common–but not only–reason why people are admitted for psychiatric inpatient care [16]. In theory, admission to hospital is a valid and meaningful outcome measure that is routinely recorded by mental health services.

### 1.6. Aim

The aim of this study was to test the feasibility of extracting and linking administrative psychiatric inpatient and nurse data to test the association between the mental health nurse to comprehensive nurse ratio and patient readmission within 12 months of discharge. If feasible, we will develop a protocol for an appropriately powered observational study.

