### 2.1. Study Setting

Our feasibility study will be conducted in two participating settings, one in South Australia (rural) and the other in Victoria (metropolitan). The site in South Australia is the only rural health care provider in South Australia with a specialised inpatient mental health facility and mental health rehabilitation service. The psychiatric inpatient unit has six beds.

The site in Victoria is a major public health provider in Melbourne. The site has two adult acute inpatient wards and provides a range of community mental health services (for example, mobile outreach service and case management). We chose two sites to test if our study is feasible in different states of Australia as well as in rural and metropolitan areas.

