### 2.12. Nurse-Level Data

#### Roster Data

Roster data will be extracted from CHRIS21 and Kronos for the time period 6 January 2020 through 5 March 2020. System Performance Support [21] defined a roster as a timetable that specifies the number of nurses and their classifications required for each shift. Data on the training nurses have received will be extracted and coded: 1. Mental health nurse, 2. Comprehensive nurse, 3. Enrolled nurse, 4. Nursing assistant, 5. Student nurse. Nurse unit managers will be asked to extract and code data from the shift roster about whether nurses have mental health nursing qualifications. We estimate that data extraction and coding should take no more than four hours of a nurse unit manager’s (NUMs) time. We will check with NUMs during the conduct of the study if the tasks were overly burdensome. We defined a mental health nurse as a registered nurse with a formal educational qualification in mental health nursing. A comprehensive nurse is a registered nurse with a formal educational qualification in general/comprehensive nursing and does not hold a formal mental health nursing qualification. An enrolled nurse is a nurse with a certificate or diploma qualification in nursing and is registered as an enrolled nurse. First level nurse refers to mental health and comprehensive nurses. Second level nurses are enrolled nurses. These data will be entered onto a data extraction form available as Supplementary Document (Table S3).

We will use the total number of nurses working each day as the denominator and then calculate the ratio of 1. Mental health nurse to comprehensive nurse, 2. Registered nurse to enrolled nurse, 3. Qualified nurse to unqualified staff.

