### 2.24. Data Analysis

#### Describing the Data

Our final data set will be at an individual patient level. Continuous data (e.g., age, length of stay) will initially be described using means and standard deviations. Categorical variables (e.g., gender) will be reported as numbers and proportions. We will use tables to summarise the characteristics of study participants (nurses and patients).

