### 2.25. Calculating Nursing Skill Mix

Each patient will have an individual row in the dataset. For each day (07:00 to 06:59) that the patient is in hospital, we will calculate the total number of registered nurses, unqualified nurses, mental health nurses, comprehensive nurses, enrolled nurses, student nurses, nursing assistants, and total number of patients on the ward. We will use these data to compute the following skill mix ratios on a day-by-day basis:○Mental health nurse to comprehensive nurse.○Qualified nurse to nursing assistant.○All nurse (including nursing assistant) to patient.○Mental health nurse to patient.○Comprehensive nurse to patient.

To compute the final skill mix measure, we will calculate averages for the duration of their admission, using days of admission as the denominator. For example, to calculate the comprehensive nurse to mental health nurse ratio. we would perform the following calculation. A patient was in hospital for three days. On the first day, there were eight comprehensive and two mental health nurses who provided care. On the second and third days, respectively, there were nine and ten comprehensive and three and four mental health nurses. This would give us a skill mix ratio of comprehensive to mental health nurses of 3:1.

To calculate nursing hours per patient day, we will total the number of nurses working on a given day, multiply by seven days and then divide by the number of patients on the ward at midnight.

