### 2.26. Inferential Analysis

We will not make inferences from our data because this is a feasibility study.

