## 3. Results

Nurse and patient data will be summarised in tables.

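### Feasibility is the study's only question, yet no planned output measures extraction or linkage, and the missing-data rules delete or impute the records that would show it

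*Protocol article*

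**What the plan says.** Section 1.6 (Aim) states the purpose: "The aim of this study was to test the feasibility of extracting and linking administrative psychiatric inpatient and nurse data". It attaches a consequence: "If feasible, we will develop a protocol for an appropriately powered observational study". Section 2.1 gives the question a second dimension: "We chose two sites to test if our study is feasible in different states of Australia as well as in rural and metropolitan areas".

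The outputs are described in four places:
- Describing the Data (section 2.24): "We will use tables to summarise the characteristics of study participants (nurses and patients".
- Section 2.25, on skill mix: "We will use these data to compute the following skill mix ratios on a day-by-day basis". The ratios are then averaged over each admission, and nursing hours per patient day are added.
- Section 2.26: "We will not make inferences from our data because this is a feasibility study".
- Section 3 (Results): "Nurse and patient data will be summarised in tables".

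Two further elements bear on feasibility. Under Roster Data (section 2.12) the authors write "We estimate that data extraction and coding should take no more than four hours" of a nurse unit manager's time, and they will ask managers whether the work was too burdensome. Section 2.23 examines the pattern and mechanism of missing data.

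Section 2.23 also names readmission and nurses' educational preparation as the two key variables. Records missing either are deleted listwise if the data are judged missing completely at random. Data judged missing at random are multiply imputed, and data judged missing not at random are deleted listwise. The Limitations section says that hospitals hold no information on the education of agency nurses.

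**The concern.** A feasibility study needs a feasibility result. Here the aim asks how well two data sources can be extracted and joined, while the outputs describe the people in the joined file. No stated output is a share of admissions, shifts or ward-days extracted, linked or complete, either overall or by site. Nothing says what finding would count as not feasible.

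The missing-data rules make this more than an omission. They are written for an association analysis, and they remove or fill in the incomplete records. For a feasibility question those incomplete records are the finding. Almost any outcome could then be called feasible afterwards, and a larger study could be launched without knowing how often the exposure or the outcome was unavailable.

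**Working it through.** The document states no sample size, target completeness or feasibility threshold, so there is no figure of its own to reproduce. The check sets the sections side by side and then adds arithmetic that is marked as illustrative.

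**1. Aim against outputs.**

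| What the aim asks | What the plan reports |
|---|---|
| Can data be extracted? (1.6) | Characteristics of nurses and patients (2.24, 3) |
| Can they be linked? (1.6) | Skill mix ratios for admissions that were linked (2.25) |
| In both states, rural and metropolitan? (2.1) | No comparison by site |
| At acceptable burden? (2.12) | Managers asked; no recording of hours stated |
| Proceed or not? (1.6) | No criterion |

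**2. The reason given for deletion.** Section 2.23 justifies listwise deletion on the ground that records without the outcome or without nurse education cannot contribute to the association between them. Section 2.14 (Data Storage) says that no formal test of association is intended, and section 2.26 rules out inference. The rule serves an analysis that the study will not run.

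**3. What the rule does to completeness.** Suppose 100 eligible admissions, of which 60 have both key variables (assumed figures).
- True completeness: 60/100 = 60%.
- After listwise deletion: 60/60 = 100%.
- After imputation: 100/100 = 100%.

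The last two figures would be 100% whatever the first one was. Deletion does lower the reported n, but that shows the loss only if the eligible number is reported beside it, and the article does not list that as an output.

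**4. The agency-nurse gap.** Each patient's daily ratio is built from ward counts for that day (2.25), so one nurse of unknown education affects every patient on the ward. In day one of the article's own example there are eight comprehensive and two mental health nurses, a ratio of 8/2 = 4. Suppose two of the eight were agency nurses of unknown education and their records were dropped. The ratio becomes 6/2 = 3. It still computes, and no planned output would mark the day as incomplete.

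**5. Precision at the small site.** The rural unit has six beds (2.1), and the window from 6 January to 5 March 2020 is 60 days. At full occupancy that is 6 × 60 = 360 bed-days. Admissions ≈ 360 / mean stay, where the mean stay is assumed. The exact (Clopper-Pearson) 95% intervals for about 90% linked are:

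| Assumed mean stay | Admissions | Linked | Exact 95% interval |
|---|---|---|---|
| 20 days | 18 | 16 (89%) | 65% to 99% |
| 12 days | 30 | 27 (90%) | 73% to 98% |
| 7 days | 51 | 46 (90%) | 79% to 97% |

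A bare percentage from the rural site would hide this width, and section 2.26 read literally could be taken to exclude the interval.

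**The case against.** The strongest reply is that this is a journal article. Completeness counts, linkage rates and progression criteria may sit in a full protocol or analysis plan that is not shown. That would settle the matter if the article were merely silent. It is not: it specifies Little's test, the imputation steps, outlier handling and a worked ratio, and it fixes a missing-data rule that works against the aim. That rule can be judged as written.

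Several stronger readings are tempting, and the document does not support them.
- *The study cannot answer its question.* Building patient-level rows from different record systems at two sites would itself show that extraction and linkage are possible in a basic sense. What is lacking is an answer that is defined in advance and can be reproduced.
- *The plan only produces tables, and only after incomplete records are dropped.* Skill mix is calculated, the missingness pattern is examined and burden is checked. Data missing at random are imputed, and gaps in non-key variables that are missing completely at random are handled pairwise. The article does not say that the tables follow deletion, nor that missing counts will go unreported.
- *Four hours is too short for a 60-day roster.* A nurse's qualification could be coded once and reused. The number of managers sharing the work is not given, nor is it said whether the daily patient count is included. The estimate cannot be called wrong; it can only be measured.

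It is also fair to say that the document offers no basis for particular percentage cut-offs. A rule that ignored the disclosed agency-nurse gap could fail a site for a reason already known.

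**Conclusion.** The point holds in this form: the plan states a feasibility aim with a conditional next step, but ties no measure of extraction, linkage or completeness to it. Its rules for the two key variables delete or impute the evidence. Followed as written, the analysed set would not show how complete extraction and linkage were, and the plan gives no pre-specified, reproducible answer on feasibility.

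No single number expresses the size, because neither the expected admissions nor a target is given. The structural part needs no assumption: after deletion or imputation, completeness of the key variables is 100% by construction. The precision figures rest on assumed mean stays of 7 to 20 days and full occupancy at the rural unit. They show only that an interval is needed there. The matter is worth correcting before the analysis, since it decides what the study can conclude.

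**What to change.** Make the feasibility measures the primary result. Report them by site, on all eligible records, before any deletion or imputation:
- (a) the proportion of eligible admissions with 12-month readmission status known;
- (b) the proportion of ward-days with complete roster, education code and patient count, with gaps due to agency nurses counted separately;
- (c) the proportion of admissions with both readmission status and skill mix linked for the whole stay;
- (d) logged manager hours, set against the four-hour estimate.

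Give exact 95% confidence intervals for (a) to (c), and state in section 2.26 that these intervals are not excluded. In section 1.6, have the investigators set in advance what result counts as feasible, allowing for the known agency-nurse gap and the small rural site. The deletion and imputation rules of section 2.23 can stay for the descriptive skill mix summaries, provided they apply only after these counts are made.

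The cost is some wording, extra counts and a time log. The real consequence is that the study could then return an unfavourable verdict.

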## 2. Materials and Methods

This is an observational data linkage study. We have structured our manuscript according to the Strengthening the Reporting of Observational Studies in Epidemiology (STROBE) guidelines (see Table S1). Our study was registered with the Australian and New Zealand clinical trial registry: ACTRN12619001337167p on 30 September 2019.

Most previous studies have determined skill mix (e.g., the nurse-to-patient ratio) using a self-report questionnaire, e.g., [8] that asks nurses to estimate the number of nurses and patients present during their last shift. The validity of this measure of skill mix has not been established and is likely subject to multiple sources of bias (social desirability, non-response). The approach we are testing in this study relies on linking data from administrative datasets together, which may be a more valid approach to estimating skill mix.

### 2.1. Study Setting

Our feasibility study will be conducted in two participating settings, one in South Australia (rural) and the other in Victoria (metropolitan). The site in South Australia is the only rural health care provider in South Australia with a specialised inpatient mental health facility and mental health rehabilitation service. The psychiatric inpatient unit has six beds.

The site in Victoria is a major public health provider in Melbourne. The site has two adult acute inpatient wards and provides a range of community mental health services (for example, mobile outreach service and case management). We chose two sites to test if our study is feasible in different states of Australia as well as in rural and metropolitan areas.

### 2.2. Participants

We will retrospectively extract administrative data on adult psychiatric inpatients diagnosed with any mental disorder who were inpatient for at least 24 h. Data on nurses working in the participating clinical service during the study period will also be extracted. Patients and nurses will be included in the study if they meet the following inclusion criteria.

### 2.3. Inclusion Criteria (Patients)

Aged 18 years or older.Diagnosed with any mental disorder.Admitted as a psychiatric inpatient for at least 24 h from 6 January 2020 to 5 March 2020.

### 2.4. Inclusion Criteria (Nurses)

All registered first level, second level nurses, nursing assistants and student nurses working on participating mental health inpatient units across all shifts (morning, afternoon, and night) from 6 January 2020 to 5 March 2020.

### 2.5. Data Sources

Participating hospitals have different patient and human resource administration systems. Consequently, we anticipate that slightly different procedures will be required to extract and code the data:○Patient-level data:
■South Australian hospital (Integrated South Australian Activity Collection (ISAAC)).■Victorian hospital (Cerner).○Nurse-level data:■South Australian hospital (Complete Human Resource Information System [Chris21] and paper shift roster).■Victorian hospital (Kronos and paper roster).

### 2.6. ISAAC

ISAAC is an electronic patient administration system that records details of public psychiatric inpatient hospitalisations [17]. Data are entered by hospital staff throughout the period of hospitalisation.

### 2.7. Cerner

The electronic patient record system used by the Victorian hospital is called Cerner and is an extensively used system.

### 2.8. Chris21

Chris21 is a self-service payroll and human resource software package that allows managers, human resources personnel and employees to enter timesheets, review and request leave [17,18].

### 2.9. Kronos

Kronos is a suite of workforce management tools [19]. Employee demographic information, hours worked, and periods of leave are all recorded in the system [19].

### 2.10. Patient-Level Data

From the relevant electronic patient records, we will extract and code (details of how we will code in parentheses) the following variables: Age (age in years at point of hospital admission), gender (coded: 1. Male, 2. Female, 3. Other), employment status at the point of admission (coded: 1. Employed, 2. Unemployed, 3. Student, 4. Retired, 5. Other), primary psychiatric diagnosis (coded: 1. Mood and/or anxiety disorder [including bipolar], 2. Schizophrenia, 3. Personality disorders, 4. Other [specify]), psychiatric comorbidities (coded: 1. Yes, 2. No), substance use (coded: 1. Yes, 2. No), physical comorbidities (coded: 1. Yes, 2. No), date of admission (dd/mm/20yy), detained under mental health law (coded: 1. Yes, 2. No), on a Community Treatment Order prior to admission to hospital (coded: 1. Yes, 2. No), when was the patient discharged from the participating ward? (dd/mm/20yy), Discharged on a Community Treatment Order (coded: 1. Yes, 2. No), admitted by inpatient psychiatric services at the participating hospitals within 12 months of discharge (coded: 1. Yes, 2. No), number of psychiatric admissions during the study period, Health of the National Outcome Scales (HoNOS) total score on admission to hospital, HoNOS total score immediately prior to discharge (recorded as number). Health of the Nation Outcome Scales (HoNOS) is a clinician rated tool comprising 12 simple scales assessing behaviour, impairment, symptoms and social functioning for those in the 18–64 years old age group [20]. We will request the unit managers to extract information on the total number of inpatients on the ward at morning handover (07:00 am) each day between the 6 January 2020 and 5 March 2020 (60 days). The patient data extraction form is available as Supplementary Document (Table S2).

